## Methods

### Overview

This study uses an observational before and after design. The choice of TERMA was a pragmatic one, as it was being implemented in the clinic. However, the research design, including research questions, outcome measures, and methods of analysis, was not influenced by the clinic. The project was registered on ClinicalTrials.gov (NCT05932108) before starting the study. The protocol complies with the Standard Protocol Items: Recommendations for Interventional Trials (SPIRIT) [30,31], and the results will be reported according to established recommendations.

### Participants and Setting

Participants meeting the study’s inclusion criteria will be recruited from the Sahlgrenska University Hospital in Gothenburg. The forensic psychiatric clinic consists of 96 patient rooms, of which 12 are allocated to the high-security ward and 84 are dedicated to rehabilitation wards. The layout includes shared spaces such as a common room, a communal dining area, and a kitchen. Due to a shortage of health care rooms, some patients share rooms. In total, staff, comprising nurses, assistant nurses, psychiatrists, and other various professional occupations, amount to approximately 290 people. These various professional categories collaborate within health teams to formulate comprehensive health care plans and treatment strategies. The study encompasses both patients and staff within the forensic psychiatry setting. The inclusion and exclusion criteria for patients and staff are presented in Textbox 1.

Textbox 1.Inclusion and exclusion criteria.
**Inclusion criteria (patients)**
Men and women aged ≥18 years committed to rehabilitation unitsPlaced under the jurisdiction of the Mental Care Act (1991:1129) on Forensic Psychiatric CareUnderstand (speak and read) SwedishAssessed by the treating physician as mentally able to understand and consent to the studyWilling to participate and sign a consent form
**Exclusion criteria (patients)**
Minors (aged ≤17 y)Treated under legislation other than the jurisdiction of the Mental Care Act (1991:1129) on Forensic Psychiatric CareCannot understand and speak Swedish and are thus unable to understand the study materialNot assessed by the treating physician or assessed and deemed mentally unable to participate in researchUnwilling to participate
**Inclusion criteria (staff)**
Men and women aged ≥18 years working within forensic psychiatric inpatient careUnderstand (speak and read) SwedishWilling to participate and sign a consent form
**Exclusion criteria (staff)**
Not directly involved in patient care within forensic psychiatric inpatient facilitiesCannot understand and speak Swedish and are thus unable to understand the study material of the studyUnwilling to participate

### Enrollment

All patients in the included wards will be assessed for eligibility by a member of the research team together with the ward staff and the responsible physician. Eligible patients will be given information about the study and asked to participate. Patients will be informed, both orally and in writing, that participation in the study is voluntary. They will also be assured that they can withdraw their consent at any time, and their decision to participate or not will not affect their care. Patients who indicate their willingness to participate will be issued a consent form. When returning the completed consent form, patients will receive the E13 questionnaire, which will include a randomly assigned identification number to ensure confidentiality throughout the research process.

All staff will be assessed for eligibility by a member of the research team. Eligible staff will receive detailed information about the study and be invited to participate. Information will be provided both orally and in writing. Staff who express their willingness to participate will be provided with a consent form. Upon returning the completed consent form, staff will receive 2 questionnaires (the E13 and the Organization Values Questionnaire [OVQ]), each coded with a randomly assigned identification number to ensure confidentiality throughout the research process.

### Design and Implementation of the TERMA Model

The TERMA model originates from Norway and has been used within both inpatient and outpatient psychiatric care. When it was first introduced in Sweden, it was given the name the Bergen model after the city it was developed in. At this time, it was adopted to align Swedish health care laws and adjusted to clarify a theoretical nursing approach. The Bergen model offers a specialized framework for managing aggression and violence within both inpatient and outpatient forensic psychiatric care [15]. After the evaluation of the Bergen model by Bergendahl et al [15], the model was adopted by another clinic in Sweden; further modifications were made; and the original name from Norway, TERMA, was reintroduced.

The core objective of the TERMA model is to proactively prevent aggression and violence by using a tiered system of low-intensity interventions, which are stratified based on the patient’s aggression level, risk of violence, and history of violent acts.

The TERMA model is rooted in the principles of compassionate health care and emphasizes treatment, communication, and effective management.

The foundation of TERMA acknowledges the inherent capabilities of all individuals, each possessing a unique self-awareness; distinct life experiences; expectations; needs; preferences; and available resources such as talents, interests, and education. Within TERMA, a central element involves a collaborative partnership between health care professionals and patients. They work together to formulate a personalized treatment plan, drawing upon the patient’s individual illness history and collectively identifying potential obstacles to effective care.

The TERMA model is structured in a “cascading” order, wherein the response to violence or aggression escalates if the interventions at one level do not prove enough.

These levels are designed to correspond with specific situational demands and environmental factors, optimizing their relevance and applicability. The *primary level* centers on the patient’s daily behavior and overall health status. It involves proactive measures aimed at understanding the patient’s emotional state, as well as managing stress and anxiety. Building trust and establishing balanced roles are key components at this stage. At the *secondary level*, the focus shifts to risk assessment and violence management. The aim is to cultivate mutual understanding between the patient and health care workers regarding the situation. The emphasis is on finding common ground and agreeing on acceptable solutions while preparing for further escalation if necessary.

When violence becomes inevitable, the *tertiary level* is activated. Here, the primary goal is to create a calm and secure environment for the patient, other patients, and staff. Clear leadership and low-intensity approaches are vital for diffusing tension, and physical restraint, if required, is executed with precision. Following the resolution of the situation, a situational analysis is offered to the patient to enhance understanding and prevent future incidents.

The implementation of TERMA is conducted through a staff training program consisting of 8 seminars. The seminars are divided into 4 theoretical sessions and 4 practical training sessions. The staff members first receive theoretical knowledge, followed by hands-on practice in restraint and self-defense techniques. This mixed format facilitates a holistic understanding of TERMA and equips staff with the skills necessary for implementation. The TERMA intervention will be uniformly implemented across all wards of forensic psychiatry at the Sahlgrenska University Hospital.

### Quantitative Sources and Collection of Data

Data will be collected from questionnaires, medical records, and administrative registers. Questionnaire data will be obtained from both patients and staff at baseline and 6- and 12-month follow-up. To assess perceived safety, data will be gathered from both patients and staff members using the E13 [15]. The E13 assesses self-reported safety, feelings of security, and violence preventative culture within the hospital wards. Respondents will be presented with 13 statements, and their level of agreement will be rated on a 4-point Likert scale, ranging from (1) “completely disagree” to (4) “completely agree,” with an additional “do not know” option available [15]. The questionnaire assigns a value of “1” to response options 3 and 4 for all items, except for the 3 negative items (items 4, 8, and 12), where a value of “1” is assigned to options 1 or 2 [15]. All other responses are scored as “0.” Thus, the sum score range for each questionnaire was 0‐13 [15].

The OVQ will be used to investigate the organizational culture in the wards. The survey will only be distributed to staff. The OVQ is based on the concepts of the competing value framework, which measures the 4 dimensions within each business: collaboration, creation, competition, and control [20]. These values compete in a very real sense for a business’s limited resources (funding, time, and people). The questionnaire contains 52 items, each rated on a 10-point Likert scale from “disagree” to “strongly agree” [20]. Data regarding incidents of threats and violence, patient and occupational injuries, and the application of coercive measures will be extracted from medical records and the local clinical registry known as MedControl PRO. These data points will be collected in 3 distinct phases: before the introduction of TERMA, at the 6-month juncture following implementation, and upon the culmination of a 12-month period. For staff members, supplementary descriptive data will be collected through a dedicated questionnaire, while background information pertaining to patients will be retrieved from their medical records.

### Outcomes

The primary outcome will be change in perceived safety reported by both patients and staff, as measured by the E13 scale total score (0‐13), between baseline and 6- and 12-month follow-up assessments. Secondary outcomes include changes in organizational culture, as measured by the OVQ and its subscales between baseline and 6- and 12-month follow-up assessments. Correlation between E13 and OVQ scores at baseline, 6-month follow-up, and 12-month follow-up will be analyzed. The number and severity of aggression incidents from 1 year before baseline to 1 year after conclusion of the study will be analyzed.

### Statistical Analysis

Descriptive statistics and comparative statistics will be used in the analysis. All data will be analyzed at a group level and reported using means and SDs. To analyze changes between the measurements, the plan is to use dependent sample 2-tailed *t* tests (if data are normally distributed) or the Wilcoxon signed-rank test (if data are not normally distributed). Regression models will be used to explore the relationship between organizational culture and the outcome of the implementation of TERMA. *P* values will be considered statistically significant if they are <.05.

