### Objectives

There is a lack of evidence regarding the effects of de-escalation models such as the TERMA model. Therefore, the aim of this project is to evaluate the violence prevention model TERMA regarding adverse events and perceived safety by patients and staff within forensic psychiatric inpatient care. In addition, the project will investigate whether the organizational culture influences the implementation of the TERMA model and the experiences of patients and staff in situations involving threats, violence, and the use of coercive measures. The project includes the following research questions:

To what extent does the implementation of TERMA impact the perceived safety and perception of violence preventative culture in the wards of staff and patients in a forensic psychiatric inpatient setting?What is the effect of implementing TERMA on the frequency of incidents of aggression and violence, health care and occupational injuries, and the use of coercive measures in a forensic psychiatric inpatient setting?How does the organizational culture of a forensic psychiatric inpatient unit impact changes in perceived safety, incidents of aggression and violence, health care and occupational injuries, and the use of coercive measures?How do patients perceive threatening and violent situations, exposure to coercive measures, and the implementation of TERMA in a forensic psychiatric inpatient setting?What are the attitudes and perceptions of staff toward working with TERMA, how do they respond to threatening and violent situations, and what is the impact of these factors on the work environment in a forensic psychiatric inpatient setting?

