## Results 

Recruitment of participants began in July 2023 and concluded by the end of 2024. Collection of data from patient and staff questionnaires will be completed 13 months thereafter. Data from administrative registries will be collected retrospectively for the entire period. Data collection and analysis of quantitative data are expected to be completed by early 2026. Collection of data for the qualitative studies is planned for the second half of 2025 and 2026, and analysis is planned for 2026 and 2027. Results from this project will be published in peer-reviewed scientific journals and presented at international conferences.

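### For incidents, injuries and coercive measures the only tests of change named are paired before/after tests without trend or exposure terms, so a running trend or occupancy change cannot be separated from a TERMA effect

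*Protocol article*

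**What the plan says.** The second research question (Introduction, Objectives) begins "What is the effect of implementing TERMA on the frequency of incidents of aggression and violence" and goes on to health care and occupational injuries and coercive measures. The Overview states: "This study uses an observational before and after design". The section on the TERMA model adds: "The TERMA intervention will be uniformly implemented across all wards of forensic psychiatry". No ward is left as a comparison.

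Under Statistical Analysis, "All data will be analyzed at a group level and reported using means and SDs". Change between measurements is to be tested with a two-tailed paired t test, or with the Wilcoxon signed-rank test if normality fails. Regression is named only for relating organizational culture to the outcome of the implementation.

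The time basis of the incident data is described in more than one way:
- Quantitative Sources and Collection of Data has incidents, injuries and coercive measures collected in three phases: "before the introduction of TERMA, at the 6-month juncture following implementation, and upon the culmination of a 12-month period".
- Outcomes states: "The number and severity of aggression incidents from 1 year before baseline to 1 year after conclusion of the study will be analyzed".
- Results states: "Data from administrative registries will be collected retrospectively for the entire period".

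Outcomes makes the E13 total score primary. Besides the OVQ, it lists the number and severity of aggression incidents. Injuries and coercive measures, which research question 2 names and the data collection section covers, are not listed there.

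**The concern.** Research question 2 is an effect question in a single clinic without a control. The only thing that can stand in for what would have happened without TERMA is the course of the same series before implementation. A paired comparison of a period before with a period after ignores that course. It attributes to the period difference whatever was already changing: incident rates, reporting habits or the number of patients on the wards. Room numbers do not fix exposure either, since Participants and Setting says that some patients share rooms.

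At stake is whether the answer to research question 2 can be interpreted. The error can go either way: a trend already falling would look like a benefit, and a trend already rising would mask one.

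**Working it through.** **No figure of the plan to reproduce.** The article states no incident rate, ward count, trend, occupancy or power for these outcomes. Everything numerical below is an illustration on assumed inputs.

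**Step 1: expected ratio with no TERMA effect.** Let the log incident rate change by b per month, and compare 12 months before with the 12 months directly after. Each later month lies 12 months after its counterpart, so the rate ratio is exp(12b):
- b = -0.01: exp(-0.12) = 0.887, an apparent fall of 11%.
- b = -0.02: exp(-0.24) = 0.787, an apparent fall of 21%.
- b = -0.03: exp(-0.36) = 0.698, an apparent fall of 30%.

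With the sign of b reversed, the ratio is the reciprocal. At b = +0.02 it is exp(0.24) = 1.27, so a true rate ratio of 0.79 would show as about 1.00. Occupancy acts in the same way: if patient-days fall to 90% and the rate per patient-day is constant, raw counts show a ratio of 0.90.

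**Step 2: false positives, wards as pairs.** Assumed: 8 wards, 2 incidents per ward-month, negative binomial dispersion 0.5, 12 months on each side, no TERMA effect, two-sided 5% level. Ranges are across repeated simulations.

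| Trend per month | Paired t test significant | Segmented negative binomial significant |
|---|---|---|
| 0 | 5% to 7% | 4% to 7% |
| -1% | 9% to 11% | 4% to 5% |
| -2% | 28% | 5% to 6% |
| -3% | 48% to 53% | 5% to 6% |

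The Wilcoxon test, run once in this set-up, gave 4%, 9%, 24% and 44%.

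**Step 3: a different set-up.** Poisson monthly counts for the whole clinic, 12 month-pairs, no TERMA effect, with assumed base rates of 5, 10 or 20 incidents per month. Share of runs in which the paired t test is significant:

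| Scenario | 5/month | 10/month | 20/month |
|---|---|---|---|
| No trend | 5% | 5% | 5% |
| -10% per year | 8% | 11% | 20% |
| -20% per year | 20% | 33% | 60% |
| -30% per year | 44% | 72% | 95% |
| Occupancy falls to 90% | 8% | 11% | 18% |
| Occupancy falls to 80% | 18% | 33% | 56% |

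Segmented Poisson regression with a log-exposure offset (joint test of level and slope change) stayed between about 3% and 6% throughout.

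**Step 4: what the better method costs.** Under the assumptions of step 2, with no trend and a true 30% fall, the segmented model with known dispersion detected the effect in 16% of runs (joint test) or 22% (level change alone), against 46% for the paired t test. The standard error of the log level change was about 0.31. An estimate of 0.70 then has a 95% CI of exp(ln 0.70 ± 1.96 × 0.31), roughly 0.38 to 1.28.

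**Step 5: the data basis.** Three phases support only a phase contrast. A window opening 1 year before baseline, extracted for the whole period, supports a pre-implementation slope. The end of that window also needs a definition. Results puts the end of questionnaire collection 13 months after the end of 2024 and expects quantitative collection and analysis to be complete by early 2026. If the study concludes with the last questionnaire, 1 year later is about early 2027.

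**The case against.** The strongest reply is that the paired tests may not be meant for incidents at all. Statistical Analysis does not name incidents, and Outcomes words change between assessments for E13 and OVQ, while the incident sentence stands apart and names no test. A count model for a non-primary outcome is often left to an analysis plan. This has some force: the paired tests reach incidents only through the reference to all data and to changes between measurements. But the article fixes a summary for all data and offers no other method for an effect question that it poses itself. A plan that follows it inherits the problem.

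Several stronger readings are tempting and are not supported:
- A reader might infer that only three snapshots will exist and that the time series is thrown away. Outcomes and Results describe a longer window. What can be shown is that the sections disagree and that no named method uses the series.
- A reader might infer that any trend will appear as a TERMA benefit. A rising trend would hide one, and at -1% per month the excess of false positives in step 2 is small.
- A reader might infer that patient turnover rules out pairing. The Introduction gives a median care duration of 7.5 years in Sweden, so turnover within a year may be modest, and wards or months could be paired. The article simply does not state the unit.

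Two practical objections stand. Segmented regression loses a good deal of power (step 4). And TERMA comes in through eight seminars, so a sharp break on one date is doubtful.

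**Conclusion.** The concern holds in this limited form. For research question 2, the tests of change that the article names cannot separate a pre-existing trend or an occupancy change from a TERMA effect, in either direction, and the sections disagree on the time basis of the data. That conclusion follows from the design and the stated method, on the reading that the statement about all data includes incidents. The size does not follow from the documents: the 0.79 ratio and the false-positive rates of about 28% (-2% per month), about 10% (-1% per month) and near 5% (no trend) depend on an assumed trend, and the percentages also on assumed wards, rates and dispersion.

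This should be fixed, but it does not undermine the study's main result, because the primary outcome is E13 and the article openly describes an observational before/after design.

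**What to change.** 1. Reconcile Quantitative Sources and Collection of Data, Outcomes and Results in favour of the full window, and define when the study concludes.
2. For incidents, injuries and coercive measures, replace the paired tests with an interrupted time series count regression (negative binomial or overdispersed Poisson) on monthly counts. Include a log patient-days offset (staff hours for occupational injuries), a pre-implementation slope, and level and slope change at a stated TERMA start. Treat the seminar roll-out as a transition period. Report rate ratios with 95% CIs instead of means and SDs.
3. List injuries and coercive measures as secondary outcomes in the Outcomes section.
4. State that events coinciding with the TERMA start remain a source of confounding that this model cannot remove.

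No extra recruitment is needed. The costs are clearly wider intervals and lower power than a naive before/after test, some analyst time, and the work of obtaining monthly patient-days and staff hours from administrative records. The article mentions neither these denominators nor event dates, so their availability should be confirmed before the model is fixed, and the model should be fixed before the incident data are analysed.

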## Introduction

### Background

Aggression and violence are common within forensic psychiatric inpatient care, encompassing verbal and physical threats, as well as escalations that may result in physical injuries [1,2]. A meta-analysis found that 17% of patients in psychiatric inpatient care had been involved in at least one incident of interpersonal violence [3], and research indicates that the proportion is even higher, exceeding 20%, in forensic psychiatric inpatient care [4]. Studies from forensic psychiatric care report a higher prevalence of patients who are violent compared to acute care settings and general psychiatric hospitals [5]. Several factors could contribute to the escalation of aggressive incidences in forensic psychiatric inpatient care, including shortage of staff; insufficient knowledge or practice in aggression management; and changes in patient demographics, prevalence of mental health disorders, treatment approaches, and institutional policies [5].

In psychiatric (inpatient) care, aggression and violence have traditionally been seen as linked to mental illness and other individual patient characteristics. Therefore, response has centered on reactivity and control, and staff education has emphasized self-defense, control, and restraint techniques. However, over the last 2 decades, focus has shifted toward seeing aggressive patient behavior as a result of a complex interplay of diverse internal, external, and situational factors. Violent behavior may lead to injury but may also have other consequences, such as diminished therapeutic relationships [6], lower job satisfaction, and increased psychological stress [7,8]. Previous research on staff and patient experience of aggression and violence that resulted in coercive interventions (including seclusion, restraint, and medication) shows that incidents negatively affect treatment, work environment, job satisfaction, and therapeutic relationships between patients and staff [9]. Research also indicates that structured de-escalation models increase active listening between staff and patients that helped reduce seclusion and coercive methods within the ward [10]. In addition, the use of coercive measures as a response to violent behavior is problematic for both patients and staff and harmful for the therapeutic alliance. Moreover, patients experience these measures punitively [9].

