In Sweden, someone having been found guilty of a crime committed under the influence of a severe mental disorder can be sentenced to forensic psychiatric care instead of prison. Forensic psychiatric care is compulsory, and the sanction is not determined by time, as stipulated by the Swedish Courts’ Forensic Mental Health Act. Recent measurements indicate that the median care duration is 7.5 years but can be even longer [23]. Patients within forensic psychiatric care in Sweden represent a highly heterogeneous group [24]. Most common diagnoses include different forms of psychotic disorders, substance use disorders, and personality disorders. Comorbidity is prevalent, and 2 or 3 concurrent diagnoses are very common [25]. A large proportion of patients in forensic psychiatry are offenders who have committed violent crimes, and consequently, they present a distinctive set of challenges related to aggression and violence [24,26].

Delivering health care services within the framework of mandatory care poses challenges, including amotivation, noncompliance, and impediments to trust between patients and staff [27]. The indefinite duration of care adds complexity to the task of establishing a secure health care environment [23]. Forensic psychiatric inpatient care confronts these challenges and requires adaptation to ensure the effective implementation of treatment and the resulting discharge [28]. Violence and aggression are prevalent in forensic psychiatric inpatient care [3], posing a complex challenge that requires innovative and evidence-based interventions [4,16]. Current recommendations advocate for a proactive rather than a reactive approach to dominate staff education [29].

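### Incident counts: group-level means with paired tests suit skewed counts repeated within patients poorly, and if period totals are paired the false-positive rate can far exceed 5%

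*Protocol article*

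**What the plan says.** The second research question (Objectives) asks what implementing TERMA does to the frequency of aggressive and violent incidents, injuries and coercive measures. The Outcomes section adds the number and severity of incidents, from one year before baseline to one year after the study ends. Incidents are not the primary outcome; that is the E13 total score.

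The Statistical Analysis section gives one approach for everything: "All data will be analyzed at a group level and reported using means and SDs". Change is tested with a paired t test if the data are normal, "or the Wilcoxon signed-rank test (if data are not normally distributed". Regression is named only for the link between organizational culture and the outcome of implementation. The section does not say whether the pairs for incidents are patients, wards or calendar periods.

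Three other statements bear on the point. The Background reports that "17% of patients in psychiatric inpatient care had been involved in at least one incident of interpersonal violence" and that "research indicates that the proportion is even higher, exceeding 20%, in forensic psychiatric inpatient care". Participants and Setting gives the size: "The forensic psychiatric clinic consists of 96 patient rooms", of which "84 are dedicated to rehabilitation wards". It adds: "Due to a shortage of health care rooms, some patients share rooms".

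**The concern.** Incidents are counts with many zeros and a long right tail, and one patient can contribute many. A group mean and SD describe such data poorly. If a minority of patients produces most incidents, the clinic total can move a long way because one or two of them improve, deteriorate, leave or arrive.

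A paired test needs several pairs, and one clinic total before against one after is a single pair. The group-level instruction therefore invites splitting totals by month or ward. Successive months then contain largely the same patients. The scatter between months within a year does not show how much patients' rates drift from one year to the next, so the standard error can be too small. At stake is whether the published answer on incident frequency reflects TERMA or the course of a few individuals.

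**Working it through.** The article gives no incident rate, event count or power calculation, so there is no figure of its own to reproduce. Every incident rate below is an assumption.

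**1. How many patients might be involved (illustration only).** The forensic proportion from the Background times rooms from Participants and Setting:
- 0.20 × 84 = 16.8 and 0.20 × 96 = 19.2, so about 17 to 19.
- The 20% is stated as a lower bound. At an assumed 25% to 30%: 0.25 × 84 = 21.0 up to 0.30 × 96 = 28.8.
- At the general psychiatric 17%: 0.17 × 84 = 14.3 and 0.17 × 96 = 16.3.

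**2. Period totals paired, no TERMA effect.** Assumptions: 96 patients; yearly counts negative binomial with mean μ and shape k; 20% with at least one incident. Solving (1 + μ/k)^(−k) = 0.80 gives k = 0.155, 0.089 and 0.064 for μ = 0.5, 1 and 2. Twelve monthly totals before are paired with twelve after, and a paired t test is run at 0.05.

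| Mean incidents per patient per year | Rejection, rates redrawn each year | Rejection, rates stable |
|---|---|---|
| 0.5 | about 31% | about 5% |
| 1 | about 55% | about 5% |
| 2 | about 70% | about 5% |

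A repeat run gave 30%, 53% and 70% for redrawn rates. The Wilcoxon test was nearly identical (31%, 54%, 69%), so the fallback does not help here.

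**3. One patient, period totals paired.** The clinic has 4 incidents a month in both years, plus one patient adding 2, 3 or 4 a month in the before-year only. The paired t test reports a fall in 51%, 83% and 96% of runs. With a base of 8 a month the figures are 32%, 58% and 81%.

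**4. Patients paired.**
- Type I error under the assumptions of step 2 is about 4% to 5% for both tests.
- If only one patient changes, by any amount, paired t gives p = 0.32; if two change equally, p = 0.16. The Wilcoxon test with two non-zero differences cannot go below p = 0.50 and needs at least six of the same sign to pass 0.05.
- An effect can be hidden in the t test. Take 84 patients. Fifteen fall from 3 to 1 (15 × 2 = 30 fewer), two rise from 3 to 18 (2 × 15 = 30 more), and the rest stay at zero. Totals are 51 and 51. Paired t gives p = 1.00 and Wilcoxon p = 0.025. With those two differences set to zero, paired t gives p < 0.001.
- With 20% involved and independent years, 0.80 × 0.80 = 64% of pairs are zero in both periods; with stable rates the share is higher. The Wilcoxon test gains nothing from these pairs.

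**The case against.** **SAP detail.** This is a condensed article, and the model, exposure offset and sensitivity analyses usually sit in an SAP. That is fair for their absence alone. But the article does not leave incidents open: it assigns a level, a summary and two tests to all data. Group level may partly mean that no individual will be identifiable, and it does not prove that monthly totals will be paired. The result in step 2 is therefore conditional on that pairing.

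**Stronger readings that the documents do not support.**
- *A fixed number of 16 to 19 patients produces every incident.* The percentages are background literature with no time window, one is from general psychiatry and the other is a floor. Rooms are shared, so rooms do not count patients. The data also cover threats, injuries and coercive measures, so more patients may contribute.
- *The standard error is too small by a factor of 2.1 to 5.7.* That factor belongs to a Poisson standard error, which the plan does not use, and it needs patients' rates to be redrawn between periods. Paired tests take their spread from the observed differences.
- *One or two patients can create significance under any pairing.* Not when patients are paired, as step 4 shows.

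**Stable rates.** If each patient's rate stays the same across years, monthly pairing holds about 5%. Long stays ("the median care duration is 7.5 years but can be even longer") favour the same patients being present in both years. They do not show that a patient's rate of violence is constant over that time.

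**Excluding active patients.** Making a claim depend on the result without the most active patients would be selection on the outcome. According to the section on the TERMA model, interventions are graded by aggression level, violence risk and violent history, so these are patients it targets. This objection stands and limits the remedy.

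**Conclusion.** The concern holds for the secondary incident outcome only. The stated analysis suits these data poorly, and its consequence depends on a pairing that the article does not fix. With monthly totals, false positives run from about 5% (stable patient rates) to about 31% to 70% (rates redrawn each year, which is the pessimistic end). With patients paired, the test is valid, but the t test can miss an effect because of a few extreme counts, and most pairs tell the Wilcoxon test nothing. These sizes rest on assumed values: 96 patients, 20% involved, mean 0.5 to 2 incidents per patient per year, and negative binomial counts. The direction follows from the structure of the data; the exact size in this clinic is unknown.

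**What to change.** In the analysis plan, take incidents out of the all-data rule and state the following:
- **Unit and model:** the patient is the unit. Use a negative binomial (overdispersed) count model with a patient random effect or patient-clustered standard errors, period as the covariate of interest, and log days on ward as offset.
- **Descriptive result:** report the number of distinct patients with at least one incident in each period, beside the incident counts.
- **Sensitivity analysis:** show the result without the most active patients. This is descriptive and not a condition for claiming an effect.

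The cost is some plan wording and extra analysis work, and possibly a wider confidence interval for the incident result. Medical records are already a named source and registry data are collected retrospectively, so new collection should not be needed. Incidents taken from the local registry must carry a coded patient identifier; the article does not say whether they do, and this should be confirmed before the extract is made.
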